## **B. Secondary outcome measures**

As for Secondary and other outcome measures, the following outcome were evaluated at baseline, 12 weeks, and one year (52 weeks) later.

- a: QOL questionnaire: SGRQ total domain difference 12 weeks after the baseline.
- b: QOL questionnaire: SGRQ domain other than Total domain (Symptom, Activity, Impact).
- c: The 6-minute walk test (6MWT) assesses dyspnea on exertion using the modified Borg Scale (Material D), walking distance, lowest oxygen saturation level, highest pulse count, and lower limb fatigue measured with the modified Borg Scale.

\*Evaluate the difference 12 weeks and one year (52 weeks) after the baseline.

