## **C. Other outcome measures**

- a. Nutritional measures: ① BMI (Body Mass Index), ② serum prealbumin, ③ serum albumin, ④ hemoglobin, ⑤ Midupper Arm Circumference (MAC), ⑥ Triceps Skinfold thickness (TSF), ⑦ Arm Muscle Circumference (AMC), ⑧ Arm Muscle Area (AMA), ⑨ grasping power.

\* Skinfold thickness measures to assess changes in fat mass using Harpenden skinfold calipers (Holtain) according to its standard methodology. Measurement is performed on the non-dominant hand, and in the case of paralysis, on the non-paralyzed side. We evaluate the average value of the three measurements. The measurement of TSF performs as follows. Subjects are in a lateral decubitus position, the upper arm was flexed by 90 ° at the elbow joint, a mark was placed at the midpoint between the shoulder bladder projection and the ulnar olecranon projection, the skin 1 cm away from the mark was picked up to so that the fat layer is separated from the muscle, and we measure the thickness by sandwiching the marked part with a caliper. As for the measurement of SSF, with the patients in the lateral decubitus position, the same method as TSF is used at the portion of the shoulder blade lower corner. For MAC, the surroundings of the part mark for TSF is measure with a measuring tape. AMC and are calculate by this formula:  $[AMC(cm)=MAC-3.14 \times TSF(cm)]$  and  $[AMA(cm)=(MAC-3.14 \times TSF)2/4\pi]$ , respectively.

- b: MMRC (modified Medical Research Council) dyspnea scale (Material E)

- c: Frequency and severity of acute aggravation of COPD are evaluated by dedicated daily records. The diary will be self-filled and will be submitted to an independent evaluator after the study period.

Contents of daily records \* Definition and Evaluation of acute aggravation: Severity scale (Material F)

Type 1 (sever): 3 major items are found

Type 2 (moderate): 2 major items are found

Type 3 (mild): 1major with any minor items are found

Major Items:

- (1) Obvious worsening of dyspnea, (2) Obvious increase of sputum purulence,
- (3) Obvious increase of sputum quantity

Minor Items:

- (1) Upper respiratory tract infection lasting more than 5 days, (2) Fever without other obvious cause, (3) Increased wheezing,
- (4) Increased cough, (5) Respiratory rate or heart rate increased more than 20%.

In addition, we evaluate the number of unscheduled outpatient visits and hospitalizations associated with exacerbation of COPD.

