#### • **Statistical Analysis**

1. Handling of cases and target group for analysis

In this study, cases enrolled in clinical trials and excluding dropouts will be the main analysis group.

2. Method of analysis

In this study, based on data analysis is performed by setting two analysis groups, FAS (Full Analyze Set) and PPS (Per Protocol Set).

FAS and PPS are defined as follows.

FAS: All assigned patients except for dropped out patients

PPS: Patients who achieved 40 or more acupuncture treatments in one year, excluding dropout patients.

Distributions of all the outcome measures at baseline are shown.

For the primary outcome measures, the secondary outcome measures, and other outcome measures, ratios or means of the differences between baseline and 12 weeks and between baseline and 52 weeks are calculated.

For all outcome measures, we look at the changes of variables in 12 weeks (from baseline to 12 weeks later) and in 52 weeks (from baseline to 52 weeks later). And then, for main outcome measure and secondary outcome measures, we compare these 12-week-change and 52-week-change using the analysis of covariance (ANCOVA) with baseline values and GOLD classification as covariates and treatment group as the factor of interest.

For the change from baseline in other outcome measures, an independent sample t-test is use.

Continuous variables and ordinal variables are shown as the means (standard deviation), and their significant differences are shown by 95% confidence intervals (CI) and p-values (significance level 0.05). Count variables are shown as the number of counts and percentages, and X2 test or Fisher's exact test results are shown with p-values (significance level 0.05).

For the changes in arterial blood oxygen saturation and in pulse during the 6-minute walk, we use the mixed effects model to analyze the difference between the 12-week-change and 52-week change. In this mixed effects model, the fixed effects are groups and times, the interaction terms are group x time, the intercept of random effects is individual, the slope is time, and the estimation method is the maximum likelihood method.

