**7. Enrolling Criteria of research subjects.**

Patients with COPD to be included in this study are those who are diagnosed with COPD according to Global Initiative for Chronic Obstructive Lung Disease (GOLD) by NHLBI/WHO workshop report, who are able to visit the hospital as outpatients and fulfill the following criteria.

- **Inclusion criteria**

1. Patient diagnosed as COPD and able to visit as outpatient.
2. Patient who had been judged as stable condition by the physician.
3. Those who were rated as grade 1 or more according to MRC criteria.
4. Those who were classified as stage II or more advanced to GOLD criteria.(Material F)

“Stable” here means when a COPD patients were clinically stable with no history of infections or exacerbation of respiratory symptoms and no changes in medication within the 3 months preceding the study outset, and had no signs of edema.

- **Exclusion criteria at the onset of the study**

1. Those who have heart failure (The cor pulmonale is excluded), collagen disease (RA and PM/DM, etc.), malignant tumor, or severe mental disorders.
2. The patient who were in concurrent respiratory rehabilitation program.

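### Exacerbation, unscheduled-visit and hospitalisation counts are assigned a change-from-baseline t-test although no baseline is recorded for them, and the alternative rule for counts names no unit

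*Protocol*

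**What the plan says.** Protocol, Outcome Measures, C. Other outcome measures, item c: "Frequency and severity of acute aggravation of COPD are evaluated by dedicated daily records". The same item adds that "we evaluate the number of unscheduled outpatient visits and hospitalizations associated with exacerbation of COPD". The diary is completed by the patient and handed in once the study period is over.

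Protocol, B. Secondary outcome measures, on timing: "As for Secondary and other outcome measures, the following outcome were evaluated at baseline, 12 weeks, and one year (52 weeks) later". Material A-2 (study design schedule) differs. It ticks the diary at weeks 1, 12 and 52 only, whereas SGRQ, the walk test and the other repeated measures also have a tick at week -1.

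Protocol, Statistical Analysis: "For all outcome measures, we look at the changes of variables in 12 weeks", and likewise over 52 weeks. Then: "For the change from baseline in other outcome measures, an independent sample t-test is use". A separate sentence reads: "Count variables are shown as the number of counts and percentages, and X2 test or Fisher's exact test results are shown", at the 0.05 level.

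Protocol, section 7, defines a stable patient as one with "no history of infections or exacerbation of respiratory symptoms and no changes in medication within the 3 months preceding the study outset".

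Both analysis sets (FAS and PPS) leave out dropouts. The multiple-imputation sensitivity analysis covers primary and secondary outcomes only. Under Criteria of Intervention Cancellation, item 3, hospitalisation for acute aggravation is one ground on which acupuncture can be cancelled.

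**The concern.** These outcomes are counts of events that can recur in one patient over a year. The rule written for their outcome class needs a baseline value, and the schedule does not collect one. The other rule that could apply does not say what is being counted, so the choice between two different analyses stays open until the data are in.

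Neither rule takes account of how long each patient was observed. Both run in sets from which dropouts are removed, and no sensitivity analysis brings those patients back for this outcome class. A serious exacerbation can itself lead to the end of acupuncture, and only one arm receives acupuncture. The route out of the analysis could therefore depend on the outcome and differ by arm. What is at stake is how far the exacerbation and hospitalisation results can be trusted.

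**Working it through.** **1. The passages side by side**

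| Place | What it implies for the diary counts |
|---|---|
| B. Secondary outcome measures (timing) | measured at baseline, 12 and 52 weeks |
| Statistical Analysis | change from baseline for every outcome; t-test on that change for other outcomes |
| Material A-2 | diary at weeks 1, 12 and 52; nothing before treatment |
| Section 7 | no exacerbation in the preceding 3 months |

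The first two need a baseline and the third does not collect one. By the fourth, a 3-month look-back would give zero exacerbations for every patient. Subtracting that constant changes nothing, and the 3-month window does not match a 52-week count. The protocol does not say that baseline should be set to zero.

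**2. Arm sizes**

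The protocol gives no event rate, dispersion or power for these outcomes. Its SGRQ sample size (difference 10, SD 10, two-sided 0.05, power 0.8) reproduces: the t-test calculation gives 16.7, so 17 per arm, with power 0.807 at 17. The checks below use 17 per arm (after dropout) and 22 per arm (enrolled).

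**3. Type I error under each reading**

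Assumptions, since the documents give no figures: negative binomial counts with mean μ per patient-year and dispersion k (variance μ(1 + kμ)), equal follow-up, no treatment effect. Simulated at nominal 5%, with μ from 0.3 to 2.0 and k from 0 to 2:

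- Chi-square on patients with at least one event: 4.1-5.8%.
- Fisher's exact test on the same unit: 1.3-2.7%.
- t-test on raw counts (baseline taken as zero): 3.9-5.1%.
- Chi-square on event totals: 4.1-5.2% at k = 0, and higher once k is above 0.

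For the event-total reading the statistic is (a - b)²/(a + b), where a and b are the arm totals. Overdispersion multiplies its expected size by about 1 + kμ, so the error is approximately P(|Z| > 1.96/√(1 + kμ)):

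| μ | k | 1 + kμ | 1.96/√(1 + kμ) | Approximation | Simulated, 17 and 22 per arm |
|---|---|---|---|---|---|
| 0.8 | 0.5 | 1.40 | 1.66 | 9.8% | 10.1%, 9.7% |
| 1.5 | 0.5 | 1.75 | 1.48 | 13.8% | 13.6%, 14.0% |
| 0.8 | 1.0 | 1.80 | 1.46 | 14.4% | 14.5%, 14.7% |
| 1.5 | 1.0 | 2.50 | 1.24 | 21.5% | 20.6%, 21.7% |

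**4. Bias if cancelled patients leave the analysis**

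Let h be the share of exacerbations that lead to hospitalisation, p the chance that a patient has at least one, and q the share of such AG patients who are excluded, with no matching exclusion in UG. All are assumptions. Then p = 1 - (1 + kμh)^(-1/k). With identical arms, the apparent AG/UG hospitalisation ratio is (1 - q)/(1 - qp).

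- μ = 0.8, k = 1, h = 0.1, q = 0.5: p = 1 - 1/1.08 = 0.074; ratio = 0.5/0.963 = 0.52.
- μ = 1.5, k = 0.5, h = 0.2, q = 0.25: p = 1 - 1.15^(-2) = 0.244; ratio = 0.75/0.939 = 0.80.

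Over μ 0.8-1.5, k 0.5-1.0, h 0.1-0.2 and q 0.25-0.5, simulation gives ratios of 0.52-0.80 for hospitalisations and 0.83-0.97 for all exacerbations, with no true effect.

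**5. Candidate models under the null, equal follow-up**

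- Quasi-Poisson with a t reference (μ 0.5-1.5, k 0-2): 2.3-5.0%.
- Negative binomial, Wald test, with a three-level GOLD covariate (assumed 40/40/20; μ 0.8 or 1.5, k 0.5 or 1): 5.1-7.2%, with 0.4-20% of fits not converging.
- Poisson with robust standard errors, same settings: 6.4-8.8%.

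**The case against.** Four things can be said on the other side.

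- **The generic sentences are not meant literally for every item.** Patients' expectations are also listed among the other outcomes and are measured at baseline only, so they have no change score either. This is fair, but it does not settle which rule governs the diary counts.
- **The t-test can be computed.** With baseline taken as zero it becomes a t-test on raw counts and holds its level when follow-up is equal. This stands. A reader might infer that the analysis is impossible; the accurate statement is that no measured baseline exists and the protocol does not supply the substitute.
- **The chi-square rule does not generally produce false positives.** A percentage and Fisher's exact test both need a denominator, so patients are the natural unit, and there the error is near or below nominal. This also stands. The inflation needs the event-total reading together with overdispersion, and the documents establish neither.
- **Cancelling acupuncture is not the same as dropping out.** The protocol never equates them. A reader might infer that severe exacerbators in AG will be removed; the text allows it but does not say it. Leaving dropouts out also limits unequal follow-up.

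Detailed modelling of such an outcome is often left to a statistical analysis plan, and none is shown. Here, however, the protocol does state a rule, and that rule does not fit the data it collects.

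**Conclusion.** The point holds as an internal contradiction plus an undefined unit. The change-from-baseline rule covers counts for which the schedule records no baseline, and it is unclear which of two rules applies. This follows from the text alone.

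The consequences are conditional. Counting patients costs information on repeat events but not error control. Counting events would give a type I error of about 10-21%, but only under the assumed 0.8-1.5 events per patient-year and overdispersion 0.5-1.0; without overdispersion it is about 5%. The bias towards acupuncture arises only if cancelled AG patients are handled as dropouts, and its size rests wholly on assumed inputs.

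These are neither primary nor secondary outcomes, and the 52-week SGRQ conclusion does not depend on them. The correction should be made because it is cheap and removes a choice that would otherwise be made after the data are seen.

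**What to change.** - Exempt exacerbations, unscheduled visits and hospitalisations from the change-from-baseline rule, and bring the timing sentence into line with Material A-2.
- Compare events per patient over observed diary time, using a rate model that allows for overdispersion and has log person-time as offset. Quasi-Poisson with a t reference is one option, and negative binomial another if it converges. At 17-22 per arm, negative binomial was not shown to control error better than the simpler choices, so the reason for a rate model is its use of repeat events and observation time.
- Include all randomised patients up to their last diary day, including those who stop acupuncture.
- If chi-square or Fisher's exact test is kept, state that the unit is patients with at least one event.
- Collect the diary when a patient stops early, not only after the study period.

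The cost is a few sentences, one extra model and earlier diary collection for some patients. Sample size and the primary analysis do not change.

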#### • **Statistical Analysis**

1. Handling of cases and target group for analysis

In this study, cases enrolled in clinical trials and excluding dropouts will be the main analysis group.

2. Method of analysis

In this study, based on data analysis is performed by setting two analysis groups, FAS (Full Analyze Set) and PPS (Per Protocol Set).

FAS and PPS are defined as follows.

FAS: All assigned patients except for dropped out patients

PPS: Patients who achieved 40 or more acupuncture treatments in one year, excluding dropout patients.

Distributions of all the outcome measures at baseline are shown.

For the primary outcome measures, the secondary outcome measures, and other outcome measures, ratios or means of the differences between baseline and 12 weeks and between baseline and 52 weeks are calculated.

For all outcome measures, we look at the changes of variables in 12 weeks (from baseline to 12 weeks later) and in 52 weeks (from baseline to 52 weeks later). And then, for main outcome measure and secondary outcome measures, we compare these 12-week-change and 52-week-change using the analysis of covariance (ANCOVA) with baseline values and GOLD classification as covariates and treatment group as the factor of interest.

For the change from baseline in other outcome measures, an independent sample t-test is use.

Continuous variables and ordinal variables are shown as the means (standard deviation), and their significant differences are shown by 95% confidence intervals (CI) and p-values (significance level 0.05). Count variables are shown as the number of counts and percentages, and X2 test or Fisher's exact test results are shown with p-values (significance level 0.05).

For the changes in arterial blood oxygen saturation and in pulse during the 6-minute walk, we use the mixed effects model to analyze the difference between the 12-week-change and 52-week change. In this mixed effects model, the fixed effects are groups and times, the interaction terms are group x time, the intercept of random effects is individual, the slope is time, and the estimation method is the maximum likelihood method.

In this study, we perform the analysis without imputing missing values in the main analysis. In addition, as a post hoc sensitivity analysis, analysis of covariance will be performed with multiple imputation for the primary and secondary outcome measures, including missing data for dropouts. For dropout cases, multiple imputation is performed assuming MAR (Missing At Random), and when doing so, variables that exhibit a correlation ( $>0.5$ ) with the baseline values of each evaluation item and the missing variables are used as auxiliary variables.

All main analyses are carried out with STATA-16 (StataCorp LLC, College Station, TX, USA).

All data are entered by an independent data entry personnel not involved in the study.

A combination of machine-generated alphabet letters was assigned to each patient and then the data were randomized so that the individual patient cannot be identified in the data without the collation list. Furthermore, no patient information will be revealed to all

those involved in the study until the statistical analysis is complete.

The statistician must perform the analysis with the grouping and patient information masked.

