#### • Sample Size

1. The target number of cases is 44.
2. The sample size was found using the test of difference (two-sided) in the mean value of the difference of SGRQ (Total domain) values between before and after 52weeks of the acupuncture treatment from our preceding research results. Considering the results of our preceding research and the report on Minimal clinically importance (MCID) of SGRQ (total domain) as 4 units, setting the absolute value of the difference to be detected as 10 units, standard deviation(SD)10.0, the significance level as 0.05, and power as 0.8, the sample sizes per group was calculated to be 17 (two groups 34). This trial considers clinical effects for one year long, a certain number of dropouts is expected. Therefore, assuming approximately 30 percent (10 cases) may drop out, about 22 cases for each group is necessary (the final sample size was 44).

Table Sample size (two groups)

| $\tau$ | Power (%) | Standard deviation |     |      |      |
|--------|-----------|--------------------|-----|------|------|
|        |           | 9                  | 9.5 | 10.0 | 10.5 |
| 10     | 90        | 37                 | 40  | 45   | 49   |
|        | 80        | 28                 | 31  | 34   | 37   |
|        | 70        | 23                 | 25  | 27   | 30   |
|        | 60        | 18                 | 20  | 22   | 24   |
|        | 50        | 15                 | 16  | 18   | 20   |

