### Criteria of Intervention Cancellation

Cases to be considered as intervention cancellation

1. when a patient requests to stop acupuncture treatment
2. when the physician in charge considers further acupuncture treatment is not appropriate (including the request from patient).
3. When a patient is hospitalized due to the acute aggravation of COPD or other reasons and intervention by acupuncture treatment becomes difficult, the physician in charge or the main researcher can cancel the intervention.
4. When an acupuncture treatment facility collaborating with this research cannot

continue acupuncture treatment, the main researcher can cancel the intervention.

- **Procedure of Trial Stoppage (cancellation)**

1. During the trial period, in case the physician in charge recognizes that the safety of acupuncture treatment cannot be secured, the main researcher shall be consulted and can decide to cancel the trial.
2. If the cancellation of the trial is decided, all who are involved in this trial should be notified within one week and the trial is cancelled.

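### The set called FAS excludes every dropout and dropout is undefined, so the primary SGRQ comparison is a completer analysis open to bias

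*Protocol*

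**What the plan says.** Protocol section 6, Statistical Analysis, item 1, states that "cases enrolled in clinical trials and excluding dropouts will be the main analysis group". Item 2 names two sets. The first is "FAS: All assigned patients except for dropped out patients". The second is "PPS: Patients who achieved 40 or more acupuncture treatments in one year, excluding dropout patients". Neither contains all randomised patients.

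On missing data the same section says "we perform the analysis without imputing missing values in the main analysis". Dropouts re-enter only in one place: "as a post hoc sensitivity analysis, analysis of covariance will be performed with multiple imputation", with imputation under missing at random.

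Sample Size plans for loss, "assuming approximately 30 percent (10 cases) may drop out", within a total of 44.

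Criteria of Intervention Cancellation gives four grounds: the patient asks to stop acupuncture, the physician judges it unsuitable, hospitalisation makes it difficult, or the treating facility cannot go on. The third begins "When a patient is hospitalized due to the acute aggravation of COPD or other reasons and intervention by acupuncture treatment becomes difficult".

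Three further places matter. Protocol of the Study, step F, schedules the baseline tests again at 12 and 52 weeks and makes no exception after cancellation. Section 9 lists, among the consent items, that any patient may withdraw at any time. Period of Clinical Trial records an additional analysis dated January 2023, after the analysis concluded in August 2020.

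**The concern.** A full analysis set exists to keep the groups as randomised. Here the label is attached to a set from which patients are removed because of something that happened after randomisation. The rule governs who belongs to the set, so it is more than a by-product of missing week-52 questionnaires. A patient who completes week 12 and leaves later is out altogether, and that patient's observed week-12 SGRQ is lost even to the 12-week SGRQ comparison listed as secondary outcome a. This loss of data needs no assumption about why patients leave.

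The second difficulty is that the protocol never says what makes a patient a dropout. A patient whose acupuncture is cancelled may or may not be counted as one. If so, exclusion has routes in the acupuncture arm that usual care does not have, and one of them, hospitalisation for COPD aggravation, is plausibly linked to a worse score. Patients know their allocation and complete the primary questionnaire themselves, so loss related to outcome is a realistic possibility. At stake is whether the headline difference compares the randomised groups or only those who stayed.

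**Working it through.** **Inputs from the protocol (Sample Size):** difference 10 units, SD of change 10, two-sided 0.05, power 0.8, 17 per group (34), about 10 dropouts, total 44, MCID 4 units. Allocation is 1:1, so 22 per arm.

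**1. The plan's own figure.** The normal approximation gives n = 2(1.960 + 0.842)² × (10/10)² = 15.7, so 16 per arm. The exact two-sample t calculation gives power 78.1% at 16 and 80.7% at 17 per arm, so the stated 17 per group reproduces. All 20 cells of the protocol's table reproduce as well.

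**2. Planned exclusion.** 10/44 = 22.7% of those randomised. The stated 30 percent matches 10/34 = 29.4% of the evaluable number. The main analysis set is thus planned to omit more than one randomised patient in five.

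**3. What the exclusion could do.** The protocol gives neither the split of dropouts between arms nor their link with outcome, so both are assumed and varied. Set-up: 22 + 22 patients, change SD 10, no true effect, change coded so that a positive value is worsening. Each patient has a dropout score with correlation ρ to the week-52 change. The patients with the highest scores in each arm are removed, 10 in all, and the remainder are compared by t-test (20,000 runs, no covariates). Entries are the bias in SGRQ units (negative favours acupuncture) and the two-sided type I error.

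| Dropouts, acupuncture/usual care | ρ = 0 | ρ = 0.3 | ρ = 0.5 | ρ = 1 (extreme) |
|---|---|---|---|---|
| 5/5 | 0.0; 5.0% | 0.0; 5.4% | 0.0; 5.8% | 0.0; 10.6% |
| 6/4 | 0.0; 4.9% | -0.4; 5.2% | -0.7; 6.1% | -1.3; 13.0% |
| 8/2 | 0.0; 5.0% | -1.2; 6.4% | -2.0; 9.6% | -4.0; 31.1% |
| 10/0 | 0.0; 5.0% | -2.1; 8.9% | -3.6; 16.8% | -7.0; 56.1% |

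**4. Check by formula.** Removing a fraction q of one arm shifts its mean by ρ × SD × φ(z)/(1 − q), where z is the upper-q normal point.

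- 10/22 removed: 10 × 0.727 = 7.27 at ρ = 1, so 0.5 × 7.27 = 3.6 at ρ = 0.5.
- 8/22 removed: 5.90 at ρ = 1. 2/22 removed: 10 × 0.1636/0.9091 = 1.80. The difference at ρ = 0.5 is 0.5 × (5.90 − 1.80) = 2.05.

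Both agree with the simulation to within 0.1 unit.

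**5. Power.** With an effect of 10, SD 10 and no selection, exact power is 90.0% if all 22 + 22 give week-52 data, 80.7% with 17 + 17, 79.5% with 14 + 20 and 77.1% with 12 + 22. Keeping all randomised patients needs no larger trial.

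**The case against.** The strongest reply is that a reader might infer more than the text supports, namely that the cancellation rules generate dropout in the acupuncture arm alone and so the primary result is biased toward acupuncture. The documents do not establish this.

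- The cancellation section is about stopping the intervention. No text says that a cancelled patient leaves the study, and step F keeps the 12- and 52-week tests without exception. The 40-session condition is added to the exclusion of dropouts in the per-protocol set, which suggests that patients with few sessions can remain in FAS.
- Usual-care patients can leave too, by withdrawing consent. Loss of declining or disappointed usual-care patients would shrink or reverse the bias. The fourth cancellation ground, a facility that cannot continue, has no evident link with prognosis.
- The imputation analysis includes dropouts and takes well-correlated variables (above 0.5) as auxiliaries, so it may already draw on week-12 SGRQ. Like the usual repeated-measures model, it rests on missing at random, so that assumption alone is no reason to dismiss it.
- It might also be argued that post hoc is simply the wrong label for an analysis written into a protocol. Given the dated additional analysis, it may describe the timing truthfully.
- A statistical analysis plan, not shown, may define dropout.

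All of this stands against the claim of proven bias, its direction and a single figure for its size. It does not alter the stated rule: the protocol itself fixes the main set as one without dropouts and without imputation, and the analysis that keeps them is secondary. The missing definition leaves the harmful reading open.

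**Conclusion.** The point holds in limited form. By the protocol's own definitions the primary SGRQ comparison is a completer analysis, planned to omit about 10 of 44 randomised patients together with any week-12 data they provided. That part rests on the text alone.

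Bias is a risk and depends on two things the documents do not give. It is about zero if loss is balanced under the same mechanism, or unrelated to outcome. If loss falls mainly on the acupuncture arm and is moderately related to outcome (assumed ρ of 0.3 to 0.5), it is about 1.2 to 3.6 units toward acupuncture, with type I error of about 6% to 17%. The upper end comes close to the quoted MCID of 4. These figures come from a t-test on change without covariates, so they indicate scale for the planned ANCOVA and do not predict its result.

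**What to change.** 1. Define FAS as all randomised patients in their assigned group.
2. Define dropout, and state that cancelling acupuncture is not in itself dropout and that the week-12 and week-52 SGRQ already scheduled are still obtained. The grounds for cancellation need not change.
3. Make the primary analysis one that uses all observed data of all randomised patients. Redefining the set alone is not enough, because ANCOVA without imputation still drops anyone lacking a week-52 score. Either promote the multiple-imputation ANCOVA already described, with week-12 SGRQ always in the imputation model, or use a repeated-measures model of both visits.
4. Keep the completer ANCOVA as a sensitivity analysis and call it that. One check that departs from missing at random is optional.
5. Leave the words post hoc in place unless the imputation analysis was in fact specified before unblinding.

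If the data are already closed, items 1, 3 and 4 can still be carried out and reported with their timing stated.

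Cost: amended wording, a little more analysis, and questionnaires from patients who have stopped acupuncture. The total of 44 is unchanged. The estimate may turn out less favourable to acupuncture.
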